## Abstract

**Background:**

Glaucoma involves progressive optic nerve fibre loss, subsequently leading to irreversible and disabling visual field defects. In Europe, the prevalence of glaucoma is approximately 2.2 % of all people aged over 40 years; this equates to 12 million people. Glaucoma patients require regular lifelong follow-up, contributing to a large financial and resource burden for the National Health Service (NHS) in the UK. This study aims to determine whether providing newly diagnosed glaucoma patients with a personalised client-held eye health summary (‘glaucoma personal record’), improves patients’ knowledge of their glaucoma condition. A potential long-term benefit could be improved self-management and henceforth a slower rate of deterioration.

**Methods/Design:**

HOPE Glaucoma is a 3-year, prospective, parallel-group, pragmatic, single-centred, randomised controlled trial. An anticipated 122 adults, newly diagnosed with glaucoma (including ocular hypertension, suspected glaucoma and/or chronic open-angle glaucoma) will be recruited from a nurse-led ophthalmology outpatient clinic at a medium-sized NHS Trust. Participants will be randomly allocated to receive standard clinical care (control arm) or standard care plus a glaucoma personal record, detailing the current state of their condition (interventional arm). Participant assessments are designed to test whether provision of a glaucoma personal record 1) improves patient knowledge of glaucoma and 2) contributes to improvements in clinical outcomes, i.e. delay of visual field loss. The primary outcome measure is better client knowledge of glaucoma at the 9–12 month follow-up visit. Secondary outcome measures include the rate of visual field loss and patient-reported outcome measures on visual function (National Eye Institute VFQ – 25) measured at baseline, 9–12 months, 24 months and 36 months. Estimating a 20 % drop-out rate, the study will have 90 % power to detect a mean two-point difference in glaucoma knowledge score between groups at 5 % significance - based on two-sided Mann–Whitney *U* test.

**Discussion:**

If a glaucoma personal record is found to significantly improve glaucoma patients’ knowledge of their condition, this intervention could potentially provide a low-cost, straightforward tool to educate and engage glaucoma patients. Subsequently, this could have the potential to increase patient self-management and therefore allow glaucoma patients to prolong their sight functionality for longer.

**Trial registration:**

ISRCTN41306818, registered on 22 August 2013.

**Electronic supplementary material:**

The online version of this article (doi:10.1186/s13063-015-0863-2) contains supplementary material, which is available to authorized users.

## Background

Glaucoma encapsulates a disparate group of eye diseases that are multi-factorial and individual to each patient. The common factor is progressive optic nerve fibre loss, which leads to irreversible and disabling visual field defects if it is not diagnosed and treated early. It is estimated that in Europe approximately 12 million people are affected by glaucoma, equating to 2.2 % of the population aged over 40 years [1]. These individuals require lifelong review to monitor their condition and response to topical ocular antihypertensive eye drops and/or other treatments. As the population ages, glaucoma will continue to present a significant burden for our current healthcare resources [2]. Improved knowledge and understanding has the potential to enhance compliance and any tool which increases patients’ understanding of their glaucoma should be beneficial to all stakeholders. Beneficiaries of this research are presented in Table 1.

**Table 1 Tab1:** Beneficiaries of increased client understanding of their glaucoma

Beneficiaries	Reasons
Patients/clients	Receive appropriate knowledge, support and motivation to manage their condition to remain sighted for their lifetime.
Family and caregivers	Glaucoma can be hereditary. Significant life-changing effects to family and/or caregivers if visual loss is not prevented. If relative remains sighted for their lifetime, burden of care is reduced.
Medical and nursing staff in acute care	Clients carry an individualised summary of the current state of *their* glaucoma thus increasing communication and continuity of care.
Ophthalmic department and organisation (the Acute Trust)	Increased capacity to care for engaged glaucoma clients, resulting from good resource use and high-quality service.
General practitioners and community optometrists (primary care)	Glaucoma clients successfully self-manage their care, and can share their eye summary and health state with primary care healthcare professionals.
Local healthcare economy	Clients diagnosed with a long-term sight-threatening condition are managed within current resources, and the burden of visual disability within the community is curbed.
Clinical nurse glaucoma specialist	Job satisfaction. Professional kudos. Sense of value to all those above, but especially clients. Enjoy sharing knowledge and skills and supporting client group.

There are various client-held care records utilised throughout the UK healthcare services [3–5], yet there is a paucity of such records specifically designed for those with glaucoma. Previous research has recognised that clients who receive emotional support and information at the initial diagnosis of glaucoma benefit by displaying good compliance and co-operation with their care [6]. Individualised care of glaucoma patients, taking into account healthcare needs and patient beliefs about illness and medicines, has also been shown to improve adherence to ocular hypotensive therapy and have the potential to delay progression of the condition [7].

There is currently no available evidence of previous efforts to produce a client-held ‘glaucoma personal record’ for secondary care ophthalmic units and the authors are not aware of any research assessing whether client-held glaucoma personal records produce better health outcomes in glaucoma [8]. Clinical teams may provide numerous resources to clients, depending on the individuals’ specific needs, yet there is potential to produce a standardised summary that can be tailored to record each individual’s current appearance of their glaucoma status. This summary should add value to client care as it would be held by each individual and personalised to reflect *their* condition. One would expect that providing glaucoma clients with their own personal ‘glaucoma personal record’ or client-held eye summary, at diagnosis, may potentially help to engage them more effectively with their diagnosis and increase their understanding.

National Institute of Clinical Excellence (NICE) guidelines on the diagnosis and management of chronic open-angle glaucoma and ocular hypertension recommend that research is required to assess “what is the clinical effectiveness and cost effectiveness of providing people with ocular hypertension (OHT), suspected glaucoma (SG) and/or chronic open-angle glaucoma (COAG) with a ‘glaucoma personal record’ compared with standard treatment?” [8]. This study aims to fulfil this requirement by assessing the clinical effectiveness of providing patients with OHT, SG and/or COAG (henceforth collectively referred to as glaucoma) with an in-house developed ‘glaucoma personal record’, when compared with current standard best practice.

Clinical effectiveness will primarily be measured by assessing patient knowledge concerning his/her own condition at 9–12 months, to coincide with a regular follow-up visit in clinic. Furthermore, client perception of how their glaucoma affects daily living and ophthalmological clinical parameters will be measured annually for 3 years. The ultimate aim is to instigate methods of enhancing self-management through increased glaucoma awareness and potentially achieving deceleration of glaucoma progression in patients.

## Methods

### Trial design

This 3-year, prospective, single-centre, parallel-group, randomised, controlled clinical trial will assess the effect of graphic eye-health information provision to patients with glaucoma or risk of glaucoma.

### Participants and settings

Newly referred patients attending a nurse-led ophthalmology clinic in a medium-sized hospital in the North of England will be assessed by the chief investigator (CI), an ophthalmologic nurse specialist, for suitability using the criteria detailed below:

### Inclusion criteria

Adult (age ≥18 years)Patients newly diagnosed with glaucoma, to include the following three presentations:o ocular hypertension (OHT): intraocular pressures (IOPs) above the normal range (more than or equal to 21 mmHg), but no signs of optic nerve fibre loss or visual field losso suspected glaucoma (SG): optic nerve fibre loss or visual field loss or both in presence of normal intraocular pressureso chronic open-angle glaucoma (COAG): any combination of raised intraocular pressures, optic nerve fibre loss and/or visual field loss.o any combination of the above OHT, SG, COAGBoth primary (cause of outflow resistance or angle closure is unknown) and secondary (outflow resistance results from another disorder) glaucoma cases can be included such as pigment dispersion syndrome (PDS) or pseudoexfoliative glaucoma (PEXF)

### Exclusion criteria

Under age (<18 years)Mental incapacity through inability to read, co-morbidities (e.g*.* severe stroke, advanced dementia) or any other contributing factorInability to provide informed written consentUnable to speak or understand English since an interpreter is not available throughout the course of the study.Previous diagnosis of glaucoma

Other co-morbid ophthalmological conditions, such as cataracts and age-related macular degeneration are not listed as exclusion criteria to ensure that the study is pragmatic.

Patients meeting the eligibility criteria will be recruited into the trial by the CI from a ‘new glaucoma’ referral clinic. Recruiting newly diagnosed adults, with little or no experience of previous glaucoma services, will reduce prior experience of secondary ophthalmic care and potential educational bias.

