#### Secondary outcomes

The secondary, longer-term, outcome measure is rate of visual field loss. In line with clinical practice, visual field loss will be measured at least annually (more frequently if there is a clinical indication). The relative visual loss rates between control and intervention groups will also be measured annually. Visual field testing will be performed by standard automated perimetry (SAP) using the Humphrey Central 24–2 programme. The Humphrey perimeter provides print-outs with statistical analyses of single field-test results, including numerical indices of reliability, and deviation from the norm of age-matched visual field analyses. The visual field indices used to identify progression of visual field loss will be mean deviation (MD) from the mean. MD represents the average difference between normal age-corrected sensitivity values and the subjects’ measured values at all test points. The rate of progression of visual field loss will be measured by linear regression analysis of the MD from the mean, expressed in decibels per year (or the newer visual field index, which was not available at the start of this study).

A simple measure was selected for use in this trial. However, there are challenges to using visual field analyses to detect progression. The test is subject to variability in performance, even for the same patient. Modern perimetry attempts to reduce sources of error in, for example, reduced test time, continuous gaze/fixation monitoring. The role of the operator is crucial in assisting patients to perform the test as accurately as possible [13]. All visual field testing will be undertaken by the CI to reduce inter-assessor variability.

Trend analyses to quantify rate of visual field loss require at least five tests to detect progression. This means relatively frequent testing in the first 2 years following diagnosis, especially if patients initially present with loss. The European Glaucoma Society (EGS) suggest three tests a year in the first 2 years. As such, this secondary outcome measure will take approximately 2–5 years to establish. The MD score will be documented in the ‘glaucoma personal record’ for the intervention group, and obtained from standard medical records for the control group.

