#### Tertiary outcome

Participants’ demographic data will be collected and analysed to compare the distribution between control and intervention groups in terms of: age, gender, postcode and highest level of education achieved. The latter two are of particular relevance as the study will assess self-education and disease awareness [15]. The control and intervention groups will also be stratified by disease diagnosis (OHT, SG and COAG), although the aforementioned primary and secondary outcome measures are based on collective data.

Other potential confounding factors that will be recorded for each participant are related to general eye health and the resulting management of the newly diagnosed glaucoma. It will be recorded if patients: have never worn glasses/lenses, wear glasses/lenses due to old age (reading and/or driving), wear glasses since childhood or early adulthood due to congenital visual defect. Note will also made whether patients are prescribed IOP-lowering eye drops or undergo a laser or surgical intervention during the study period.

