### Data analysis

Patient eligibility, recruitment and retention through the study will be presented in a CONSORT flow diagram displaying the number of eligible patients, patients approached with study information, patients recruited and randomised and patients completing study follow-up. Reasons for loss to follow-up will also be presented, where known. Participant baseline details and descriptive statistical data will be tabulated to show overall recruit demographics, and any differences in distribution (e.g. patient age, sex, level of education) will be analysed by applying one-way ANOVA or chi-squared test.

The primary outcome, the degree of difference in patient knowledge about their glaucoma condition will be analysed by comparing the average scores for control patients versus the average score of patients received the glaucoma personal record. Statistical significance will be assessed by applying the Mann–Whitney *U* test. The secondary outcome, visual field loss, will be measured with a Humphrey Automated Visual Field Analyser in the ophthalmology clinic and average measurements for baseline visit and the final visit at 36 months will be compared within each group (control and intervention respectively) and also between the two groups. Depending on distribution of the data, determined by Shapiro-Wilk test, the paired *t* test or Wilcoxon test will be applied for paired samples to determine any significant changes in visual field loss. For assessing differences between the control and intervention groups, either *t* test or Mann–Whitney *U* test will be applied. Like visual field loss, the other secondary outcome measure - patient-related outcome measure VFQ-25 - will be presented as average scores. Any statistical differences will be assessed by Wilcoxon test within each group and Mann–Whitney *U* test between groups.

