## Discussion

The NICE Guideline Development Group published recommendations for research into the clinical effectiveness of providing people with COAG with a ‘glaucoma personal record’ when compared with standard treatment [8]. To the authors’ knowledge, the HOPE Glaucoma study constitutes the first effort towards fulfilling NICE recommendations and the planned publication of study findings in circa 2017 will provide the first data generated by a randomised controlled trial on ‘glaucoma personal record’ provision. Findings will strengthen the evidence base available for glaucoma management guideline development and may have a positive impact upon the future education and care of glaucoma patients.

Strengths of the trial include the use of a time-matched control, the random allocation of the ‘glaucoma personal record’, allocation concealment to minimise selection bias, long-term recruit follow-up (36 months) and the use of validated questionnaires to capture outcome data. Due to its fairly pragmatic approach, the trial is not without limitations. The decision not to collect detailed data on patient co-morbidities could omit potential confounding factors throughout this trial. Other foreseeable study limitations include a limited patient demographic, due to recruitment from a single-centre in a rural location with a limited ethnic variety. The generalisability of trial findings may also be limited by the selection of participants from a nurse-led clinical nurse specialist new glaucoma referral clinic only. Gray et al*.* [9] indeed found that the depth of information provided for newly diagnosed patients varied across clinics and between individual clinicians. Despite this limitation, the use of one glaucoma practitioner throughout the duration of the trial offers a means of standardising the type and quality of information and materials given to all participants at diagnosis and during follow-up review. Variability in the nature of the information provided at diagnosis and in the quality of outcome measure assessment will be minimised, as the CI will be responsible for the provision and adaptation of care for all participants, according to the individual clinical need, and regardless of the arm to which they were allocated.

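### With cataract and macular degeneration enrolled and lens and macular status not among the listed items, the per-arm change in mean deviation cannot be read as glaucoma progression alone (minor; the randomised comparison is not biased in expectation)

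*Protocol article*

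**What the plan says.** Five places in the protocol article bear on this.

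- **Exclusion criteria.** Other eye disease is allowed, for the sake of a pragmatic design: "Other co-morbid ophthalmological conditions, such as cataracts and age-related macular degeneration are not listed as exclusion criteria".
- **Discussion.** The limits on data collection are a stated choice: "The decision not to collect detailed data on patient co-morbidities could omit potential confounding factors throughout this trial".
- **Tertiary outcome.** The further confounders to be recorded are described as concerning the general health of the eyes and how the new glaucoma is then managed. The items named are spectacle or lens history ("It will be recorded if patients: have never worn glasses/lenses", and so on) and "whether patients are prescribed IOP-lowering eye drops or undergo a laser or surgical intervention during the study period". Lens opacity and macular disease are not named. The surgery item does not say whether cataract surgery is included, or whether eye and date are kept.
- **Secondary outcomes.** "MD represents the average difference between normal age-corrected sensitivity values" and the patient's own values, taken over all test points. The rate of loss is the regression slope of MD in dB per year.
- **Data analysis.** For visual field loss, "average measurements for baseline visit and the final visit at 36 months will be compared within each group", and the two arms are also compared with each other, by a t test or Mann–Whitney test. No adjustment for ocular co-morbidity is stated.

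The Background closes by giving slower glaucoma progression as the ultimate, hedged, aim.

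**The concern.** MD, as the article defines it, is a global index corrected for age and nothing else. Any fall in measured sensitivity lowers it, whatever the cause. A lens that clouds over three years, or a macula that deteriorates, can move MD with no change in the optic nerve. Cataract surgery can move it back up.

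The conclusion the trial hopes to draw is about glaucoma. If lens and macular status are not recorded, a reader of the results cannot tell how much of an arm's 36-month change is glaucomatous. The within-arm paired tests have no randomised comparator to cancel the other causes. Patients with ocular hypertension enter with no field loss by definition. If their glaucomatous change over three years is small, other causes could make up a large share of what is measured, and the outcomes are analysed on all diagnoses together.

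**Working it through.** **No plan figure to reproduce.** The article states no power, SD or expected difference for visual field loss. Its sample size of 122 is for the knowledge score and is used below only for numbers per arm. That cataract and macular disease lower measured sensitivity, and that cataract surgery raises it, is general ophthalmic knowledge and not taken from the article. Prevalences, slopes, jumps and the SD are all assumptions.

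**1. Slow lens or macular decline, per-arm reading.** Let p be the share affected and s their extra MD loss per year. Each arm's mean slope is the glaucoma slope g plus p × s. Assume p = 10–50% and s = 0.1–0.5 dB/year.

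- Lowest: 0.10 × 0.1 = 0.01 dB/year, or 0.03 dB over 36 months.
- Highest: 0.50 × 0.5 = 0.25 dB/year, or 0.75 dB over 36 months.
- Share of the reported loss that is not glaucoma, ps/(g + ps): for an assumed g = 0.2 dB/year, from 0.01/0.21 = 5% to 0.25/0.45 = 56%; for g = 0.5 dB/year, from 0.01/0.51 = 2% to 0.25/0.75 = 33%.

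**2. Cataract surgery, per-arm reading.** Let p now be the share operated on and d the MD jump at surgery. Assume p = 5–20% and d = 1–3 dB. The mean shift p × d runs from 0.05 to 0.60 dB (0.20 dB at 10% and 2 dB), in the direction of less loss. This is opposite to step 1, so the net direction is unknown.

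**3. Between-arm comparison, cataract surgery.** Assume an SD of 36-month change of 2.5 dB without surgery, and 49 per arm (122 × 0.8 / 2 = 48.8).

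- Base SE: 2.5 × √(2/49) = 0.505 dB.
- Added variance, p(1−p)d²: at 10% and 2 dB, 0.09 × 4 = 0.36, which is 5.8% of 6.25.
- New SE: √(2 × 6.61/49) = 0.519 dB, a rise of 2.8%.
- At 20% and 3 dB: 0.16 × 9 = 1.44, or 23% of 6.25; the SE rises by √1.23 − 1 = 11%. At 5% and 1 dB: 0.0475, or 0.8%; the SE rises by 0.4%.
- SD of the chance between-arm shift, d√(2p(1−p)/49): 0.12 dB in the central case, range 0.04–0.24 dB.
- Power for an assumed 0.6 dB difference (0.2 dB/year over three years): about 22% at SE 0.505 and about 21% at SE 0.519.

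The 20% drop-out in the Sample size section covers only the first 9–12 months, so fewer than 49 per arm may remain at 36 months. That would enlarge both SEs but leave their ratio unchanged.

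**4. Between-arm comparison, slow decline.** With 61 per arm, the SD of the chance shift at 36 months is 3s√(2p(1−p)/61), which gives 0.02–0.14 dB over the ranges in step 1. This agrees in order of size with step 3.

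**The case against.** The strongest case against is that this is a declared, reasoned choice in a pragmatic trial, conceded as a limitation, on a secondary outcome. Most of that stands. The concession is general, however: it is never linked to MD, and no mitigation is offered. Pragmatism justifies broad entry; it is not a reason to leave lens status unrecorded.

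Four stronger readings are tempting and not supported.

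- **Co-morbidity goes wholly unrecorded, and nothing could be checked later.** The article declines only detailed data. Laser or surgery is noted with no explicit restriction to glaucoma procedures, so cataract operations may be partly captured. Standard medical records exist and already supply MD for the control arm.
- **The arm comparison is biased.** Allocation is random, so disease at entry is balanced in expectation. Chance imbalance is ordinary sampling error and is already in the test's SE. The central 0.12 dB is 20% of the assumed 0.6 dB effect, but the base SE of 0.505 dB is already 84% of it. What remains is that unstratified, unblocked allocation of 122 people can leave an imbalance that the listed items cannot show.
- **VFQ-25 is contaminated in the same way.** The article uses it to measure the impact of visual deficit on daily life. Overall visual function is what it is meant to capture.
- **The per-arm change is pushed towards no loss.** Cataract growth and cataract surgery act in opposite directions, so the net sign is not established.

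It is also fair that data-form items may sit in the full protocol, and covariates and sensitivity analyses in an analysis plan; neither is shown. The point therefore rests on what the article itself states: the decision on co-morbidity data, the definition of MD and the named tests.

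**Conclusion.** The point holds as one of interpretation, with minor priority. Eyes with cataract or macular degeneration are enrolled, their status is not among the listed items, and MD does not separate causes. The within-arm 36-month change and the dB/year rate therefore cannot be presented as purely glaucomatous. Non-glaucoma decline could account for 0.03–0.75 dB of each arm's 36-month loss, with an opposing shift of 0.05–0.60 dB from cataract surgery. Both ranges rest wholly on assumed inputs; the article can neither confirm nor narrow them.

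The between-arm MD comparison stays valid in expectation. It gains a little noise, about 3% in the SE in the central case and 11% at the extreme of the assumed range, and is open to chance imbalance that the listed items cannot check. The primary knowledge outcome is untouched.

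**What to change.** Leave eligibility as it is, and:

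1. Record for each eye, at baseline, lens status (clear, cataract, already operated) and macular disease (yes or no). Record the eye and date of any cataract surgery during follow-up as its own item. For those already recruited (85% of 122, about 104 people), take these from the clinic notes.
2. Beside the planned t or Mann–Whitney test, compare 36-month MD between arms with an ANCOVA adjusted for baseline MD, lens status and macular status.
3. Report cataract surgery by arm, and add one sensitivity analysis that leaves out fields taken after cataract surgery in that eye.
4. In the report, do not describe the per-arm MD change or slope as glaucoma progression alone.

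**Cost.** A small burden of note abstraction and one model beside the planned test, which cannot itself take covariates. No extra visit, test or staff is needed. The sensitivity analysis conditions on an event after randomisation, so it can only be supportive.
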